### Assessment of safety

All adverse events will be recorded in the Adverse Event Log. Adverse events include any unfavorable change in a study participant’s physical or psychological wellbeing during the study period, which may or may not be the result of participation in the study. Adverse events will be reported to the CAMH REB if all of the following REB-defined criteria are met for an Unanticipated Problem: 1) The event is unexpected (relative to the product monograph, research protocol, and consent forms), 2) The event is related or possibly related to participation in the research, as judged by the PI, 3) The event suggests that the research places the participants or others at a greater risk of harm than was previously known or recognized. Required reporting will occur within 48 hours of the PI becoming aware of the event. Any Serious Unexpected Adverse Drug Reactions will be reported to Health Canada if all of the Health Canada-defined criteria are met: 1) The medical occurrence is serious (results in death, is life-threatening, requires hospitalization or prolongation of existing hospitalization, or is a congenital anomaly/birth defect), 2) The event is unexpected (nature or severity not consistent with information in the relevant source documents such as product monograph), and 3) It is judged by the reporting healthcare professional as a having a reasonable suspected causal relationship to the medicinal product. Where the event is neither fatal nor life threatening, required reporting will occur within 15 days of awareness of the information. If fatal or life-threatening, it will be reported within 7 days.

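### The written seriousness list for regulator reporting leaves out lasting disability, so a disabling reaction managed without admission could go unreported if staff rely on that list alone

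*Protocol article*

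**What the plan says.** The Assessment of safety section of the protocol article sets out three layers.

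- Recording: "All adverse events will be recorded in the Adverse Event Log".
- Ethics board: "Adverse events will be reported to the CAMH REB if all of the following REB-defined criteria are met for an Unanticipated Problem". Those criteria concern unexpectedness, relatedness and a suggestion of greater risk than was known. Seriousness is not among them, and the deadline is 48 hours.
- Regulator: "Any Serious Unexpected Adverse Drug Reactions will be reported to Health Canada if all of the Health Canada-defined criteria are met". Three criteria follow: seriousness, unexpectedness and a reasonably suspected causal link. Seriousness is spelled out as "The medical occurrence is serious (results in death, is life-threatening, requires hospitalization or prolongation of existing hospitalization, or is a congenital anomaly/birth defect".

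Two deadlines apply to the regulator route: "Where the event is neither fatal nor life threatening, required reporting will occur within 15 days of awareness of the information", and "If fatal or life-threatening, it will be reported within 7 days".

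Disability or incapacity appears nowhere in the article as a seriousness outcome. There is also no residual category for medically important events.

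**The concern.** Because all three criteria must hold together, the seriousness list acts as a gate: a reaction that matches none of its outcomes does not go to the regulator, however unexpected and however clearly drug-related it is. For a reaction in the participant herself that neither kills nor threatens life, the only listed way to count as serious is admission to hospital or a longer stay. Lasting disability handled in outpatient care has no entry.

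Persistent or significant disability or incapacity is ordinarily one of the seriousness categories in drug trials. At stake is whether the regulator hears of such a reaction in healthy volunteers. The question is still live, because Recruitment status and study timeline describes recruitment as continuing.

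**Working it through.** No calculation underlies this point. The check is to read the list, look for anything elsewhere that completes it, and follow the rule for one type of event.

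**Step 1: is the list closed?** The parenthesis runs through four outcomes (death, threat to life, hospital admission or its extension, birth defect) and ends with *or* before the last. It has no *such as* or *for example*. The second regulator criterion, on unexpectedness, does use *such as* when it names the product monograph as a source. The natural reading of the first criterion is therefore a complete list, although the text does not say outright that it is complete.

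**Step 2: does another section fill the gap?** No. The article gives no other definition of a serious event.

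**Step 3: follow the rule.** Take a reaction that is unexpected, has a suspected causal link to a study drug, leaves lasting incapacity, and is treated without admission.

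| Test | Result |
|---|---|
| Death | no |
| Threat to life | no |
| Admission or extended stay | no |
| Birth defect | no |
| Criterion 1, serious | not met |
| Criterion 2, unexpected | met |
| Criterion 3, suspected causal link | met |
| All three met | no |
| 7-day or 15-day report to the regulator | not triggered |
| Entry in the log | yes |
| Ethics board within 48 hours | possible, if the event also suggests greater risk than was known |

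**Step 4: how much exposure is involved?** The planned sample is 15 (Study participants). Each participant has one olanzapine visit per cycle phase and two phases, so 15 × 2 = 30 olanzapine courses of two nightly doses. Intranasal insulin is given at each of four visits (Study design), so 15 × 4 = 60 insulin sessions. These are maxima with no dropout. The article gives no event rate from which to compute an expected count of disabling reactions.

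**The case against.** The strongest reply is that the article does not contradict itself here. The list looks short only against a definition that the article names and does not reproduce. The criteria are labelled as the regulator's own, and Methods and materials says the study is approved under the regulator's purview, so an investigator may consult the actual definition and report the event anyway. The article also condenses a full protocol, its S1 File, which is not shown and may carry a longer list.

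Much of this stands, and it limits the point in three ways.

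- A reader might infer that such a reaction would certainly go unreported. The document does not support that. It supports only that the reaction could be missed if staff use the printed list alone.
- A reader might infer that the list has been shown to differ from the regulator's definition. It has not, because that definition is not available here. That disability belongs on the list rests on general drug-trial convention, and the sponsor has to confirm it.
- A reader might see a contradiction in the same event going to the ethics board and not to the regulator. There is none. The two routes use different criteria by design, and any non-serious unanticipated problem would be split in the same way.

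The condensation argument does not remove the point. The article does not leave the definition to another document. It writes one out and makes it decide whether a report is made. If the full protocol has a longer list, the published text still needs to be brought into line with it.

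**Conclusion.** The point holds in a limited form. As printed, the seriousness criterion has no entry for persistent or significant disability or incapacity, and because all criteria must be met, a reaction of that kind managed without admission could be classed as non-serious and not sent to the regulator. It would still be logged and might reach the ethics board.

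This rests on two assumptions: that staff apply the printed list without going back to the regulator's definition, and that this definition, as is conventional, includes lasting disability.

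One seriousness category is affected. Such events should be rare at no more than 30 olanzapine courses and 60 insulin sessions. Sample size, significance level and the primary analysis are untouched. It is worth correcting because the consequence for an affected event is a report not made at all, and the correction is very small.

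**What to change.** In Assessment of safety, reconcile the first regulator criterion with the definition it invokes, checking the whole list against the version in force, and add persistent or significant disability or incapacity. If the full protocol or the adverse-event records carry the same four-outcome list, make the same correction there. If they already carry the longer list, only the article needs changing.

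The cost is one phrase per document, plus whatever approval a wording change to the protocol requires. No visit, assessment or analysis changes. Since recruitment is continuing, the corrected list can apply to the remaining visits. It would also be sensible to look through the existing log once for any event that the shorter list might have left out.

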### Confidentiality

There is a potential risk of breach of confidentiality that is inherent in all research protocols. Breach of confidentiality will be minimized by the staff who will maintain research data (identified only by participant code number not related to name, or date of birth) in separate charts and a dedicated password protected electronic database. A list of participant names, their ID numbers, and information about how they can be reached will be kept in a separate locked cabinet with access only to study personnel authorized by the PI. Procedures have been established, and will be followed, to minimize the risk of breach of confidentiality. Procedures to maintain confidentially include: (1) formal training sessions for all research staff emphasizing the importance of confidentiality; (2) specific procedures developed to protect participants’ confidentiality; and (3) formal mechanisms limiting access to information that can link data to individual participants. All information obtained from participants will be kept as confidential as possible. Computer-based files/data will be entered into password-secured databases and paper-based files will be stored in a secure location. These data will only be accessible to personnel involved in the study and they will abide by confidentiality regulations of the REB. The REB will be granted direct access to the study participants’ original medical records for verification of clinical trial procedures and/or data, without violating the confidentiality of the participants, to the extent permitted by the law and regulations.

### Study management and materials

CAMH investigators will retain a participant identification code list if they need to contact participants after the study. This list will contain the complete name, identification number, address and phone number of all participants and will be held confidentially at the investigators site after completion of the study. Study data will be entered in a secure database. An eCRF/CRF will be completed for each participant enrolled in the study. A participant screening log, noting reasons for screen failure, where applicable, will be maintained for all participants. The investigator will document the obtained informed consent and record medical and psychiatric history, medications, and efficacy data in the eCRF/CRF. Clinical scales and neuropsychological assessments will be considered source documents and will be incorporated into the eCRF/CRF in a confidential manner. Study data will be entered in a secure database using Research Electronic Data Capture (REDCap) software. At point-of-entry, data values will undergo consistency edits (e.g., ID validation, range verification, duplicate detection) and personnel will be required to correct errors.

### Recruitment status and study timeline

Recruitment for this study began in May 2024 and has been ongoing ever since. At the time of this submission, a total of 25 participants have consented to the study, 13 of which have been eligible and enrolled. Three participants dropped out at various stages of their participation, six have completed their full participation, and the remaining are still actively enrolled and completing study visits. The retention and successful completion of participants speak to the feasibility of the study being conducted in this population. Recruitment is currently ongoing and is anticipated to be completed by June 2026. Results and an associated publication are expected 6–12 months following trial completion.

### Knowledge transmission and dissemination plans

The results from the current study will be presented at international conferences and published in open access journals to ensure widest reach to other qualified researchers and clinicians.

## Discussion

Females suffer the most from AP-related metabolic adverse effects. Brain insulin action is increasingly being recognized as a potential mediator of these side effects. Disappointingly, females are an underrepresented population in the field because of the complex confounding effects of monthly hormonal variations. This is the first study to explore the effect of menstrual cycle phases on the anti-insulin action of APs. Thus, this investigation has the potential to generate new knowledge in an area of significant unmet need. Demonstrating that APs disrupt brain insulin action, evidenced by inhibition of recognized effects of INI on neuroimaging measures, will provide novel insights into currently poorly understood mechanisms. Moreover, it may provide us with a modifiable risk factor that can then be targeted using brain insulin sensitizers to address the metabolic dysfunction (glucose metabolism, satiety, food choice) and possibly cognitive deficits at the earliest stages of the illness. This approach can improve the quality of life, long-term outcomes, and overall health of females suffering from SSD and its treatment consequences.

### Limitations and measures to minimize bias

It is recognized that the single-blind nature of this study is a limitation but required to ensure the proper distribution of study conditions across cycle phases. The trial is registered with a publicly available, free-to-access, searchable clinical trial registry before approaching the first participant to avoid bias selection of the reported result(s). Furthermore, study staff administering and scoring the extra-scanner cognitive assessments will be blinded to the INI/INP allocation to minimize any bias (they will not be involved in transferring the product into the nasal spray bottle).

Participants may experience mild subjective effects related to the study interventions (e.g., nasal irritation with intranasal administration or transient sedation with OLA), which could potentially compromise the single-blind design. To mitigate this, placebo conditions will be matched as closely as possible in appearance and administration, and participants will remain unaware of treatment allocation. Furthermore, a questionnaire will be completed at each visit to assess participant blinding success. Participants will be asked whether they believe they received the OLA or PL at that visit, as well as whether they received INP or INI they received prior to each MRI scan, and to rate their confidence in these judgements. The James’ Blinding Index (BI) will be calculated from these responses [52].

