**Fig 2 pone.0352262.g002:**
[figure not shown]
Summary of overall study design and visit protocol. Following screening, eligible participants will be enrolled to take part in the 2x2 crossover study. Each participant will undergo a total of four primary study visits, two per cycle phase (follicular and luteal). Participants will receive oral placebo (PL) on days 0 and 1 of the first visit of each phase, and oral olanzapine (OLA) on days 0 and 1 of the second visit of each phase. At each visit, intranasal placebo (INP) will be administered prior to scan #1, and intranasal insulin (INI) prior to scan #2. Figure created on BioRender.com.

Each of the study periods will involve a three-day protocol (Fig 2): administration of OLA 5 mg (or PL) HS on day 0, OLA 10 mg (or PL) HS on day 1, and cognitive testing and MRI scanning on day 2. There will be two MRI scans on day 2, the first following administration of INP and the second following 160 IU of INI. Administration of INP always precedes INI as the effect of insulin in the brain is known to last for 2 hours, and counterbalancing the administration of INI first will require a much longer washout period/study visit, adding participant burden.

The two acute OLA doses of 5 mg and 10 mg are chosen for reasons of practicality and safety in line with previous studies [24,39]. The INI dose is the maximum safest dose that has been administered in humans and is chosen based on earlier work in nine healthy males showing a dose-dependent relationship on regional brain activity, with the strongest effects being observed after 160 IU [27]. This dose has been shown to induce changes in the brain in females as well [40,41]. Blood samples will be drawn before and after the MRI to measure insulin spillover. Dose-dependent spillover of INI into peripheral circulation has been reported, although the observed brain responses were not correlated with this transient rise in circulating insulin [27]. OLA levels will be measured to assess adherence.

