### Randomization, blinding, and allocation concealment methods

Study staff will confirm eligibility and assign each participant a unique trial number. As all participants will receive oral PL at visit 1 and oral OLA at visit 2 of each cycle phase, no randomization of investigational products will occur. Study staff will remain unblinded to ensure accurate scheduling of visits during each phase. Both INP and INI will be administered at every MRI visit: INP will always be delivered before the first scan and INI before the second scan. Participants will be blinded to the order of these interventions and will not know whether they have received OLA or PL. Oral OLA and PL will be dispensed by the pharmacy in identical capsules packaged in blister packs. INI and INP will be transferred from their respective vials into identical, unlabeled metered spray bottles to maintain participant blinding.

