Cognitive assessments will be conducted following the administration of both INP and INI, and will include the Brief Visuospatial Memory Test–Revised from the Kaplan Functional System [46] as well as the Digit Symbol Substitution Test [47] Participants will also complete a series of questionnaires and rating scales, including the 3-day food diary, the Food Craving Scales, the Profile of Mood States (POMS) [48], the Subjective Wellbeing Under Neuroleptics (SWN) [49], the Barnes Akathisia Rating Scale (BAS) [50], and the Stanford Sleepiness Scale (SSS) [51]. Anthropometric measures will also be collected, including height, weight, waist circumference, and blood pressure.

The above procedures are repeated for a total of 4 research visits (two of which will occur during the follicular phase and two during the luteal phase).

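### The assessor blinding claimed for the cognitive tests is not delivered, because the fixed INP-then-INI order reveals the condition to anyone who knows the protocol

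*Protocol article*

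**What the plan says.** Under Limitations and measures to minimize bias, the article concedes that the trial is single-blind. It then offers a mitigation: "study staff administering and scoring the extra-scanner cognitive assessments will be blinded to the INI/INP allocation". The means is given in parentheses: "they will not be involved in transferring the product into the nasal spray bottle". No other means is stated.

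The intranasal order is set in two places. Under Study design, in the text after the Figure 2 caption: "Administration of INP always precedes INI as the effect of insulin in the brain is known to last for 2 hours". Under Randomization, blinding, and allocation concealment methods: "INP will always be delivered before the first scan and INI before the second scan". The latter section also says that "no randomization of investigational products will occur", and it limits concealment of the order to one group: "Participants will be blinded to the order of these interventions". On personnel it says: "Study staff will remain unblinded to ensure accurate scheduling of visits during each phase".

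Under Study visits 1–4 the timing of the tests is given as: "Cognitive assessments will be conducted following the administration of both INP and INI". The tests are a visuospatial memory test and a digit-symbol test, done at each of four visits. The Statistical analysis section names resting-state functional connectivity as the primary outcome.

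**The concern.** Keeping an assessor away from the bottles hides what a bottle contains. That is useful when the content could be either product. Here the content follows from whether the spray is the first or second of the day, so the bottle holds no information that the session number does not already give.

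What is at stake is the credibility of the cognitive results. Both tests are given by a person, and their administration and scoring can be influenced by what that person expects. A report that repeated the blinding sentence would credit these outcomes with a protection that the design does not supply. The same fixed order also means that any cognitive difference between the two sessions mixes insulin with practice, fatigue and elapsed time, so readers have extra reason to want the blinding described correctly.

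**Working it through.** The article gives no figure for this point, so the check sets its statements side by side.

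**Inputs**
- Planned participants: 15 (Study participants).
- Visits per participant: 4 (Study visits 1–4).
- Sprays per visit: 2, in one fixed order (Study design; Randomization section).
- Means of assessor blinding: exclusion from bottle filling only (Limitations).
- Timing of the tests: after INP and INI, without saying whether after each or once after both (Study visits 1–4).

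**Reading A: tests follow each spray.**
- Sessions per participant: 4 × 2 = 8. Planned sessions: 15 × 8 = 120.
- With a single sequence, the first session is always INP and the second always INI. For an assessor who knows the sequence, the probability of naming the condition is 1, against 0.5 for a guess under a 1:1 randomised order. Who filled the bottle does not alter this.

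**Reading B: tests are done once, after both sprays.**
- Sessions per participant: 4. Planned sessions: 15 × 4 = 60.
- Every session follows INI. There is no INI versus INP cognitive comparison, and so no allocation to conceal.

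The blinding sentence presupposes Reading A, since it would have no object under Reading B. The statement fails under both, for different reasons.

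**What the fixed order does to the contrasts (Reading A).** Let δ be the effect of insulin on a test score and p the shift from first to second session caused by repetition or time. The observed INI − INP difference is δ + p, and the two cannot be separated because the order never varies.

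The intranasal × oral contrast does not escape this. Oral placebo is always at the first visit of a phase and olanzapine at the second, so the contrast is

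(δ_OLA + p₂) − (δ_PL + p₁) = (δ_OLA − δ_PL) + (p₂ − p₁),

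where the subscripts on p denote the first and second visit of the phase. Only if p is the same at both visits does the last term vanish. If practice gains shrink with repetition (an assumption; the article is silent), p₂ − p₁ is negative and resembles olanzapine weakening a beneficial insulin effect.

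**The case against.** The strongest defence is that assessors may simply not be told the order. Participants are to be kept unaware of it, and the same could be done for assessors. This stands in part: the certainty computed above is conditional on the assessor knowing the protocol. But the article nowhere says that the order is withheld from assessors. It names only participants as blinded to the order, and the one protection it describes for assessors addresses bottle contents. The full protocol might describe more, but a fixed order would still make exclusion from bottle filling ineffective as the stated means.

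Several stronger readings are tempting and are not supported.

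- A reader might infer that the Randomization section flatly contradicts the blinding claim, because it calls study staff unblinded. That sentence gives visit scheduling as its reason and follows the statement on oral treatment. It can be read as a general rule, with cognitive assessors and the intranasal product as a specific exception. The firm conflict is between the fixed order and the claimed blinding.
- A reader might infer a particular rate of false-positive cognitive findings. The article gives no bias size, and a practice shift would arise even with perfectly blinded assessors, so it cannot be charged to failed blinding.
- A reader might infer that assessors know which session ought to look better. The hypotheses and both mixed models concern connectivity only, and no direction for cognition is stated.
- A reader might infer that the main result is compromised. Connectivity comes from MRI and is not scored by these assessors.

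It is also fair to say that the fixed order is openly justified by the duration of the insulin effect and by participant burden, and that single-blinding is already listed as a limitation. The point here is narrower: the sentence offered as mitigation of that limitation is inaccurate.

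**Conclusion.** The concern holds as an inaccurate statement about blinding on a non-primary outcome. Under Reading A, the condition is identifiable at 8 of 8 sessions per participant (120 planned) by any assessor who knows the protocol; this assumes such knowledge, which the article does nothing to exclude. Under Reading B the blinding claim has no content. The direction and size of any resulting bias in test scores cannot be derived from the article. The scoring half of the claim is weaker ground for criticism than the administration half, because nothing shows whether scorers see session labels; masked scoring can still be achieved, whereas blinded administration by staff who know the order cannot. The correction should be made, but it leaves the connectivity analysis untouched.

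**What to change.** 1. Withdraw the statement that staff administering the cognitive tests are blind to INI/INP. Report administration as unblinded and add this to the limitations.
2. Where the records allow, have a team member who did not administer the tests score forms stripped of visit, session and time, in shuffled order across participants and visits. Claim masking for scoring only.
3. State under Study visits 1–4 whether the tests follow each spray or are done once after both.
4. State that a raw INI versus INP cognitive difference will not be interpreted as a drug effect, because it is confounded with session order. Add that the intranasal × oral contrast is confounded with the fixed placebo-then-olanzapine visit order and is not a clean substitute.

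The cost is a little relabelling and shuffling of forms, some scorer time, and a stated safeguard that becomes weaker. Recruitment is ongoing, so the change can still be made. Forms from the six participants reported as having completed could be rescored in the same way if they were kept, but masked rescoring cannot change how their tests were administered.
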